#### Aim 3: missing data protocol

Given the exploratory nature of this pilot study, our primary approach to missing data will focus on descriptive assessment and transparent reporting rather than formal imputation. We will begin by identifying missing values and exploring patterns and extent of missingness across key variables. Where feasible, we will assess whether data are missing completely at random (MCAR), at random (MAR), or not at random (MNAR) to inform interpretation.

Consistent with current guidance for pilot studies, we will not use multiple imputation or other complex imputation techniques, as these require larger sample sizes to be valid and may introduce unnecessary complexity in a feasibility context. Instead, we will use complete case analysis for outcome analyses and report the number of participants included in each analysis. If substantial missingness is identified, we will describe it in detail and explore potential reasons, including participant characteristics or implementation factors, to inform future intervention refinement. All procedures will be transparently reported to support reproducibility and guide larger-scale trial planning.

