#### Aim 3: data analysis

##### Quantitative analysis of survey measures

In our analysis process, we will begin by reviewing the completeness and distributions of all variables. If any variables demonstrate non-normal distributions, we will apply normalizing transformations as required. Internal consistencies of scaled scores will be evaluated using Cronbach’s alpha to ensure reliability.

This study’s primary objective is to evaluate the intervention’s feasibility using the following indicators: Feasibility of Intervention Measure (FIM), Acceptability of Intervention Measure (AIM), Intervention Appropriateness Measure (IAM), attendance, and retention. Descriptive statistics—including means, standard deviations, and proportions—will be used to summarize these outcomes. A priori thresholds for success will be defined as a mean score of ≥ 16 out of 20 on the FIM, AIM, and IAM, representing a “good” rating. Attendance and retention rates will also be reported as proportions, with retention thresholds aligned with a minimum of 85% as an acceptable benchmark.

Secondary outcomes (e.g., body satisfaction and social media literacy) and exploratory outcomes (e.g., body appreciation and physical literacy) will be analyzed by assessing changes from pre- to post-intervention using paired-sample *t*-tests. Repeated measures ANOVAs will be used to further examine time effects and potential interactions. Age and BMI will be included as covariates in these models to enhance interpretation of between- and within-group differences.

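### Aim 3 proposes to assess whether missing outcomes are MCAR, MAR or MNAR, which observed data cannot settle, and uses complete cases whatever the answer; a mixed model plus a simple shift range would be a cheap improvement (minor)

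*Protocol article*

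**What the plan says.** The section Aim 3: missing data protocol opens by saying that "our primary approach to missing data will focus on descriptive assessment and transparent reporting rather than formal imputation". After a look at patterns and extent of missingness, it states, with the qualifier that this applies where feasible: "we will assess whether data are missing completely at random (MCAR), at random (MAR), or not at random (MNAR) to inform interpretation". It then says "we will not use multiple imputation or other complex imputation techniques", because these are held to need larger samples and to add complexity that a feasibility study does not need. What is used in their place is unconditional: "Instead, we will use complete case analysis for outcome analyses and report the number of participants included in each analysis". The section adds: "If substantial missingness is identified, we will describe it in detail and explore potential reasons, including participant characteristics or implementation factors". It names no sensitivity analysis.

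Under Quantitative analysis of survey measures, secondary and exploratory outcomes "will be analyzed by assessing changes from pre- to post-intervention using paired-sample" t-tests, followed by repeated measures ANOVAs with age and BMI as covariates. Aim 3: sample size calculation says that the pilot is not powered for significance, but that its effect sizes will be used to design and size the later trial.

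**The concern.** MAR and MNAR differ only in whether missingness depends on the scores that were not seen, given those that were. No comparison of observed values can tell them apart, so that part of the stated assessment is not feasible from the data to be collected. A check against MCAR is possible, but it is weak with so few missing children, and finding no difference does not show that the data are MCAR.

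The assessment also leads nowhere in the analysis. If a baseline difference between completers and non-completers were found, the paired t-test on completers would still be the reported result, although it can be biased in exactly that situation. The stated reason for avoiding imputation does not cover a likelihood-based mixed model, which imputes nothing and uses every observed pre and post score.

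At stake are the pre-post effect sizes carried into the next trial's sample size. The number analysed will be reported, but that number alone shows neither the direction nor the size of an error.

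**Working it through.** **Inputs from the protocol article.** N = 50 and an 85% retention benchmark (Aim 3: design; Aim 3: sample size calculation); 100% retention over two semesters in the parent programme (Aim 3: sample size calculation). **Assumed, not in the documents:** the size of any difference between missing and observed children, a pre-post correlation of 0.6, and a logistic missingness slope of 1.5 per SD.

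1. *The plan's own figure.* Half-width of the 95% interval for 85% retention: 1.96 × √(0.85 × 0.15 / 50) = 0.099. The stated ±10% is reproduced.

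2. *Number missing at the benchmark.* 0.15 × 50 = 7.5, so 7 or 8 children.

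3. *Power of a baseline comparison, completers against non-completers.* Two-sided 5% t-test, 48 degrees of freedom, noncentrality d × √(n₁n₂/(n₁+n₂)).
   - 43 v 7: √(301/50) = 2.454. Noncentrality is 1.227 at d = 0.5 and 1.963 at d = 0.8; power 0.225 and 0.486.
   - 42 v 8: √(336/50) = 2.592. Noncentrality is 1.296 and 2.074; power 0.246 and 0.529.

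4. *Shift in the mean change.* If completers change by c on average and the missing share m changed by c − δ, the mean over all children is (1 − m)c + m(c − δ) = c − mδ. With m = 0.15 this is 0.15 × 0.25 = 0.0375 SD and 0.15 × 0.5 = 0.075 SD of change. The standard error of a completer mean is about 1/√42.5 = 0.153 SD, so 0.075 is about half a standard error. With m = 0 the shift is zero.

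5. *Upper bound.* If exactly the worst-changing children were missing (normal changes), the bias would be φ(z_m)/(1 − m): 0.11, 0.19 and 0.27 SD of change at 5%, 10% and 15% missing. This is an extreme, not an expectation.

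6. *Simulation.* 5,000 pilots per mechanism, N = 50, about 15% missing, true change zero, paired t-test on completers. Bias is in outcome SDs.

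| Missingness depends on | Bias | Type I error | Baseline check significant | Bias after using all baselines |
|---|---|---|---|---|
| nothing (MCAR) | 0.00 | 4.9% | 5% | 0.00 |
| baseline score (MAR) | −0.07 | 8.4% | 86% | 0.00 |
| unseen change (MNAR) | 0.16 | 21.9% | 24% | 0.13 |

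The last column regresses change on baseline among completers and averages the prediction over all 50 baselines. With complete baselines and one post score, in a single group, that is what a likelihood-based model with unrestricted covariance estimates. Under strong baseline-dependent missingness the check usually fires, yet the plan's analysis does not respond. When missingness depends on the unseen change, the check mostly stays silent and the model removes little of the bias. The sign of the bias differs between the two mechanisms.

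**The case against.** The protocol gives this assessment a modest role. It is hedged, it serves interpretation only, and no MCAR test is named, so the power figures concern a test that the article does not propose. Reasons for absence will be explored, and these can legitimately inform a judgement on whether MNAR is plausible. Under Retention, a make-up post-intervention session is scheduled, which acts directly against missing post scores. If the parent programme's 100% retention recurs, there is no bias. The article states: "This study’s primary objective is to evaluate the intervention’s feasibility using the following indicators", and no pre-post change enters the progression criteria. Complete cases with open reporting are defensible in a pilot of 50. Similar dropout in two groups of 25 would largely cancel in a between-group comparison. A mixed model does not cure the MNAR case.

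Most of this stands and limits the point to a minor one. A reader might infer that the team will settle on a mechanism and then present complete-case changes as sound. The text does not say so: it promises the number analysed, a description of substantial missingness and its possible reasons, and it claims no conclusion from a null check. Nor do the documents support saying that the changes will be too favourable.

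Two things are not answered. The hedge does not make MAR and MNAR separable. And the progression rule itself accepts 15% loss, a level at which completer-only paired tests can be biased even under MAR, while the effect sizes are meant for later planning.

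**Conclusion.** The point holds in a limited form. The three-way assessment cannot deliver what the sentence describes: evidence against MCAR is possible, proof of MCAR is not, and MAR and MNAR cannot be distinguished. Using complete cases regardless is not an error in a pilot, but it is not the best available method for effect sizes that will inform a later trial.

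The size rests on assumptions. It is zero with full retention and about 0.075 SD of change if 15% are missing and changed 0.5 SD less favourably, which is smaller than the sampling error. The feasibility outcomes and progression criteria are unaffected. Severity: minor.

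**What to change.** 1. Replace the assessment of MCAR, MAR or MNAR with a stated working assumption (MAR given the observed scores and covariates). Keep the planned description of missingness patterns and reasons, and do not read the absence of a baseline difference as support for MCAR.
2. Analyse the secondary and exploratory outcomes with a likelihood-based mixed model on all observed pre and post scores, with the planned age and BMI covariates and without imputation, in place of the complete-case paired t-tests and repeated measures ANOVAs.
3. Because that model is valid only under MAR, show beside each effect size carried forward how it moves if missing children's change was 0.25 and 0.5 SD worse. The move in mean change is the missing share times the shift.

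The cost is a little extra analysis and a few sentences of text. No new data are needed, and the sample size does not change.

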## Discussion

Health-based interventions are more effective when they involve key community members in the planning process, as supported by various studies [67, 68]. Indeed, human-centered design is highlighted as crucial for addressing health challenges and promoting equitable healthcare solutions [69]. Previous research has shown that community members participating in co-design is effective for crafting innovative interventions, particularly in unique populations such as rural low-socioeconomic communities [62, 70]. Implementing this research design for an intervention aimed at enhancing body satisfaction among rural adolescent females has the potential to enhance the feasibility of the biopsychosocial intervention. Integrating community feedback into the intervention could foster an increased sense of acceptability within the community. Moreover, the unique feedback from the rural community may play a crucial role in addressing the gap in prior research on interventions addressing social media usage in this specific population.

Our human-centered protocol forms the basis for creating a feasible intervention in line with Phases Ia (define) and IIa (refine) of the ORBIT Model. This approach can be widely applied by researchers developing and piloting biopsychosocial interventions in school settings. Published evidence demonstrates that participatory co-design leads to effective intervention development [71, 72]. While co-design has been explored in physically active contexts involving adolescents, its application in the biopsychosocial field is still relatively new, and its application to body image and social media usage is novel [21, 22].

Our proposed methods account for the distinct needs, objectives, opportunities, and resources related to body image within the rural context, involving adolescents, parents, and teachers/administrators. This methodology aims to develop a physical activity-based intervention specifically customized for the middle and high school communities. In addressing both trial- and intervention-related feasibility indicators, our *Hoosier Sport Re-Social* protocol adheres to reporting feasibility measures in feasibility studies. This approach can contribute to future refinements in later phases of the ORBIT model.

## Data Availability

Not applicable (this manuscript does not report data generation or analysis).

## Abbreviations

BSQ: Body Shape Questionnaire
BAS-2: Body Appreciation Scale (version 2)
CAPL-2: Canadian Assessment of Physical Literacy (version 2)
GAD-7: Generalized Anxiety Disorder Assessment (7-item)
BSMAS: Bergen Social Media Addiction Scale
FIM: Feasibility of Intervention Measure
AIM: Acceptability of Intervention Measure
IAM: Intervention Appropriateness Measure
